## 8.4 Analysis Populations

All patients who signed the informed consent document will be defined as the All Enrolled Population. The Study Population will be defined as all patients who provide informed consent and complete the study procedures or in who an attempt to start the study procedures is made. The Analysis Population is defined as patients who are enrolled and complete at least two of the three pacing configurations. Patients who are enrolled but are found to have an inclusion or exclusion criteria violation or a significant Clinical Investigational Plan deviation such that the clinical interpretability of the results obtained from the patient is impacted, will not be included in the primary analysis, but will be reported in the patient disposition table. Safety will be reported on the All Enrolled Population and the primary objective will be reported on the Analysis Population.

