| Blood pressure                           | Recommended:
Codan
PVB transducer
17.8059 and
contact board
75.1068.00 | Commercially Released                     |
| Medtronic-EP catheters                   | Soloist
TORQR-CS
041865CS
041590CS
041565CS                               | Commercially Released                     |
| Medtronic- Guiding catheters             | ATTAIN 6250S
6250C
6227DEF
ATTAIN
SELECT II
6238TEL
6248DEL         | Commercially Released                     |
| CareLink® Programmer                     | 2090                                                                                  | Commercially Released                     |
| Analyzer                                 | 2290                                                                                  | Commercially Released                     |

| Component                               | Model Number                     | Investigational or market released |
|-----------------------------------------|----------------------------------|------------------------------------|
| Surgical connection cables              | 5114
5832(S)
5833
5487  | Commercially Released              |
| Adaptor                                 | 5103                             | Commercially Released              |
| Reference lead                          | Recommended:
F7830S
F7832S | Commercially Released              |
| Catheter connecting cable, 10 conductor | 05518SP                          | Commercially Released              |
| Connection Box and connectors           | 09083                            | Investigational                    |

The connection box is investigational. All other products used in the present study (leads and pacing devices) are commercially released (and CE-marked) and used within their intended purpose.

More detail on the basic components of the system:

The Medtronic TORQR or Soloist EP catheters are intended for use in diagnostic EP procedures. The catheter is designed for recording intracardiac electrograms and temporary pacing associated with electrophysiology studies.

The Medtronic Model 5388 DDD hand-held pacemaker is a dual chamber temporary pacemaker. A dual pacemaker has the ability to sense and pace in both chambers of the heart.

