### 7.4.1 Baseline visit

The baseline visit can be a stand alone visit or occur on the same day as the EP study. A subject is enrolled in the study when he/she signs the Informed Consent Form.

At this point, the patient will be assigned a subject number and is considered a subject in the investigation. The following procedures/data collection will be conducted during the baseline visit:

- Verification of all inclusion and all exclusion criteria
- Enrollment
- Subject demographics (e.g., age, gender, height, weight, race)
- Medical history (cardiovascular or related)
- Cardiovascular medications
- NYHA classification
- Blood pressure
- Left ventricular ejection fraction (within last 3 months, otherwise a new measurement should be performed)
- Multi-lead ECG (within last 3 months, otherwise a new ECG should be performed)
- Pregnancy test for women with child-bearing potential
- Echocardiographic evaluation (if available within last 3 months, otherwise not collected )
- Venous blood sample to determine heart failure severity (NTproBNP, creatinine and hemoglobin)
- Magnetic Resonance Imaging (MRI) as explained in paragraph below

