#### **7.4.1.1 Magnetic Resonance Imaging (MRI)**

Patients will undergo a baseline MRI before scheduled CRT-related surgery (i.e. is dedicated research study or EP procedure or actual CRT implant) to identify the location and transmuralty of any myocardial scar using late gadolinium enhancement-magnetic resonance imaging according to standard hospital practice. In addition, left ventricular end systolic volume (LVESV), left ventricular end diastolic volume (LVEDV) and left ventricular ejection fraction (LVEF) will be determined. MRI can be performed as standard of care or solely for the study.

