#### **7.4.2 Electrophysiological (EP) study visit**

The EP study visit can be a stand alone visit or can occur on the same day as the baseline visit. The EP study visit should take place within 3 months after the MRI has been obtained. Patients will undergo standard implant of a biventricular pacing system (Medtronic CRT or CRT-D) or will undergo an EP study before possible CRT-implant. If available in the center, a Finger plethysmography system (eg. model Nexfin, BMEYE B.V.) will be connected to one of the subject's fingers to measure the blood pressure non-invasively. In addition, a multi-lead surface ECG is collected during the whole procedure.

Pacing electrodes (cardiac leads or EP catheters) will be placed in the right atrium (RA) and right ventricle (RV). The coronary sinus will be cannulated, a venogram will be obtained and target vessels for LV stimulation will be identified. An EP-catheter ("Multi-electrode lead") or LV lead will be used for LV pacing. Also a CE-certified LV-quadrupolar lead from Medtronic, when available, can be used in the study as an alternative for the EP-catheter. The temporary LV pacing electrodes (EP catheter or LV lead) will be inserted into the coronary sinus (CS) and then sequentially into each suitable target vein.

Targeted myocardial regions for LV lead/catheter placement are: lateral or posterolateral (Standard vein), posterior (Alternative vein I) and anterior (Alternative vein II). Pacing will be performed at up to three spots simultaneously within the Standard vein - MultiSpot), covering the basal to apical locations when feasible (see figure 4). The leads placed in the alternative veins I and II will be stimulated separately or simultaneously (multi-vein; uni-spot) covering the heart circumferentially. A lateral LAO, RAO and/or AP fluoro-screen shot will be taken to document the different (temporary) lead positions.

A Millar pressure catheter or similar will be introduced via the femoral artery retrograde across the aortic valve into the LV for hemodynamic pressure monitoring. Heparin will be administered to ensure that the activated clotting time is monitored per standard hospital practice. The different pacing settings include simultaneous RV- and LV pacing and are in bipolar or unipolar mode.

The MRI-images will ascertain avoidance of pacing ischemic scar tissue. In addition, paced left ventricular QRS-width may also be used for optimal coronary sinus lead placement [33].

A

MRI

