## 7.5 Subject Exit and Withdrawal

Study Exit is defined as the moment when a subject officially stops participating in the study. The date and reason for subject exit must be reported to Medtronic at the earliest opportunity.

Reasons subject may be exited from the study include, but are not limited to:

- Study completion
- Subject did not provide consent
- Subject did not meet inclusion/exclusion criteria
- Subject chooses to withdraw (e.g., consent withdrawals, relocation to another geographic location)
- Investigator deems withdrawal necessary (e.g., medically justified, inclusion/exclusion criteria not met, failure of subject to maintain adequate study compliance)
- Subject death

Subjects will be exited from the study just before the moment of hospital discharge. This will be documented on the Study Exit CRF. There will be no further follow-up required for subjects that are exited from the study since no investigational products will be implanted or used in the study.

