**Table 4: Data Collection Requirements**

|                                                                              | Enrollment | Study day |
|------------------------------------------------------------------------------|-------------------|------------------|
| Inclusion/Exclusion Criteria                                                 | ✓                 |                  |
| Subject Informed Consent                                                     | ✓                 |                  |
| Demographics, medical history, CV medication, pregnancy test (if applicable) | ✓                 |                  |
| MRI (structural and hemodynamic)                                             | ✓                 |                  |
| NYHA class                                                                   | ✓                 |                  |
| LVEF                                                                         | ✓                 |                  |
| Surface ECG                                                                  | ✓                 | ✓                |
| Blood chemistry                                                              | ✓                 |                  |
| Venogram                                                                     |                   | ✓                |
| Non-invasive blood pressure                                                  | ✓                 | ✓                |
| Invasive blood pressure                                                      |                   | ✓                |
| LV pressure                                                                  |                   | ✓                |
| LV lead implant location (Chest x-ray)                                       |                   | ✓                |
| Unipolar and Bipolar electrograms                                            |                   | ✓                |
| Adverse events                                                               |                   | ✓                |
| Deviation Collection (as indicated, Section                                  | ✓                 | ✓                |
| Exit                                                                         |                   | ✓                |

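### Safety is reported on all consented patients, but Table 4 schedules adverse event collection only on the study day, and the text gives no start of collection

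*Combined protocol and SAP*

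**What the plan says.** **Who is counted.** Section 8.4 defines the population by consent: "All patients who signed the informed consent document will be defined as the All Enrolled Population". It then sets the reporting base: "Safety will be reported on the All Enrolled Population". Section 7.4.1 puts the start of participation at the same moment: "A subject is enrolled in the study when he/she signs the Informed Consent Form".

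**When events are scheduled to be collected.** Table 4 has two columns, Enrollment and Study day. The row "Adverse events" is ticked under Study day only. The deviations row is ticked under both. Section 7.6 places clinical data collection at enrollment and during the procedure.

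**What can happen before the study day.** Section 7.4.1 includes a venous blood sample at baseline. Section 7.4.1.1 adds a late gadolinium enhancement MRI and says: "MRI can be performed as standard of care or solely for the study". Section 7.4.2 sets the spacing: "The EP study visit should take place within 3 months after the MRI has been obtained". Section 6.3 expects participation of about 1 day to 3 months.

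**How observation ends.** Under Section 7.5, subjects exit just before hospital discharge. No further follow-up is required, "since no investigational products will be implanted or used in the study". Section 4.3 says: "The connection box is investigational". Section 6.5 says the same.

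**The concern.** A safety rate needs a numerator window that matches its denominator. Here the denominator opens at signature, while the only schedule for the numerator opens on the day of the EP study. A patient can sign, have blood drawn and a contrast MRI solely for the study, and wait weeks before the procedure. A patient can also leave before it: Section 7.5 lists withdrawal, unmet eligibility criteria and death among the reasons for exit. Both kinds of patient belong to the safety population, yet Table 4 schedules no collection for the waiting period or for patients with no study day.

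Section 8.5 raises the stakes. The interim look at about 20 patients is mainly a safety review, and an increase in expected adverse events can lead to re-evaluation of the study. Section 6.5 provides for no Data Monitoring Committee. If pre-procedure events are missed, both the final rate and the rate seen at the interim would be too low.

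**Working it through.** The plan states no adverse event rate, collection window or expected number of early exits, so there is no figure of its own to reproduce. The check is mainly a comparison of sections.

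1. **Denominator.** Sections 7.4.1 and 8.4: all patients, from signed consent.
2. **Scheduled numerator.** Table 4: Study day. That column also holds Exit, which Section 7.5 places just before discharge, so it reasonably covers the procedure through to discharge.
3. **Period between the two.** The minimum is zero, since Section 7.4.1 allows baseline and EP study on the same day. The maximum is about 3 months (Sections 6.3 and 7.4.2). Two limits apply to that maximum. The figure in Section 6.3 includes the hospital stay after the procedure. The figure in Section 7.4.2 runs from the MRI, which may be standard of care, so it is not necessarily time since consent.
4. **Could the table have shown earlier collection?** Yes. The deviations row is ticked in both columns.
5. **Is a start of collection given elsewhere?** Section 6.5 (adjudication) and Section 9 (electronic forms) mention adverse events but set no window. Section 8.5 uses the event rate without defining its period.

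**Illustration, on assumed risks only.** Let p be a patient's risk of an event between consent and the study day. With n patients, the expected number with an event is n × p, and the chance of at least one is 1 − (1 − p)^n. The documents give n = 40 in total and about 20 at the interim; p is assumed.

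| Assumed p | Expected, n = 40 | At least one, n = 40 | At least one, n = 20 |
|---|---|---|---|
| 1% | 0.4 | 33% | 18% |
| 2% | 0.8 | 55% | 33% |
| 5% | 2.0 | 87% | 64% |
| 10% | 4.0 | 99% | 88% |

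These are events that could occur in the gap, not events shown to be lost. If every patient has both visits on one day, the gap and the loss are zero.

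**Section 7.5.** The stated reason is that no investigational product is implanted or used. Table 3 lists the connection box as investigational, Section 6.5 repeats this, and the pacing protocol in Section 7.4.2 uses the box to switch pacing on and off. The reason and these passages cannot all stand. This conflict does not depend on how Table 4 is read.

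**The case against.** The strongest reply is that Table 4 is a visit schedule and not a definition of the collection window. Exit is also ticked only under Study day, yet Section 7.5 requires the date and reason of exit for every subject, including those who leave before the procedure. A Study day tick for adverse events could likewise mean that everything since consent is recorded by then. Other text points the same way. The committee in Section 6.5 reviews every event and death, with no time limit. Section 9 names adverse event data separately from visit data, and its adverse event and death forms include the date the center became aware, which suggests event-driven reporting. The choice of the All Enrolled Population itself implies that events from consent onward are wanted. The reporting rules may also sit elsewhere: Section 6.5 cites a Section 11, while the contents list stops at Section 9 plus appendices.

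Much of this stands. A reader might infer that pre-procedure events are definitely not captured, or that early exits contribute none by construction. The documents do not support either inference. A reader might also want to measure the harm by how far early exits dilute the rate. That would need an assumed number of exits, and it is a feature of any all-consented denominator: it would remain after the table was corrected if those patients had no events.

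The reply does not supply a start date for collection. A committee can review only what is collected, and recording at the study day does not explain how events are obtained from patients who never have one.

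**Conclusion.** The point holds as an unresolved mismatch between the safety population and the collection schedule. Events in the zero to about 3 months before the EP study, and events in patients who exit before it, may be missed. Any bias from such losses would lower the All Enrolled event rate and the rate seen at the interim. Its size cannot be computed from the documents.

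A reader might conclude that safety is understated as a matter of fact. That would require Table 4 to be the complete collection rule and events to have occurred in the gap; the documents establish neither. The conclusion rests on taking the table as written and on the absence of a stated start in the available text. It does not affect the primary objective or the sample size. The conflict over the connection box is real but secondary, and it adds no weight to the point about pre-procedure events.

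**What to change.** - In Table 4, tick adverse events under Enrollment as well as Study day.
- State in the text that collection runs from signed consent to study exit for every enrolled patient, and how events are obtained from those who exit before the EP study.
- Check both changes against any safety reporting section outside the available text, so that the table and the rules agree.
- Reconcile the reason given in Section 7.5 for no follow-up with the investigational status of the connection box in Table 3 and Section 6.5.

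The cost is one table tick, a short statement of the window, event forms available from enrollment, and one reconciled sentence. Sites would have slightly more events to report.

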## 8.5 Interim Analysis

One interim analysis is planned for this study after approximately 20 patients (one-half) have been enrolled. The primary purpose of this interim analysis is to review safety of study participants and the continuing validity and scientific merit of the study. The primary objective will not be evaluated (i.e the mean difference in pacing configurations will not be calculated) to minimize the operational and statistical bias that may result from performing an interim analysis. However the standard deviation between pacing configurations within patients will be calculated and compared to that used in the sample size assumptions. The study might be re-evaluated in case of deviations from assumed sample size calculations or an increase in the rate of expected adverse events. Study sites will receive information about interim results only if they need to know for the safety of their patients.

# 9 Data and Quality Management

Study visit data, adverse event data, device deficiency data and study deviations will be collected on electronic case report forms (eCRF) using an electronic data management system for clinical studies. The eCRF data will be reviewed using programmed and manual data checks. Data queries will be

made available to study centers for resolution. The data collected during the EP study visit coming from the heart, chest or finger (i.e. surface ECG, (non-)invasive blood pressure, LV pressure, unipolar and bipolar electrograms ) will be collected simultaneously on the universal data acquisition system (i.e. PORTI-system is a multi-channel ambulatory and stationary system for physiological research). The raw data from the PORTI-system will not be processed during the experiment, and no data will be used to guide patient care. The data from the PORTI-system, MRI images, echo images (if available) and venogram will be brought to the Medtronic office by attending Medtronic personnel. A copy of the data will remain at the site. Offline analyses include standard calculations of first time derivative of left ventricular pressure (filter settings), and timing between the different electrodes on the heart or on the chest. All data will be stored in a secure, password-protected database which will be backed up nightly. Study management reports may be generated to monitor data quality and study progress. At the end of the study, the data will be frozen and retained indefinitely by Medtronic.

All data shall be secured against unauthorized access. The privacy of each subject and confidentiality of his/her information shall be preserved in reports and when publishing any data.

Procedures in the CIP require source documentation. Source data is all information in original records, certified copies of original records of clinical findings, observations, or other activities in a clinical study. A source document is a printed, optical or electronic document containing source data. In case a printout is made from an electronic document containing source data, ensure this is a certified copy. A certified copy is signed and dated by study site personnel with a statement that it is a true reproduction of the original source document. In some cases items on the CRFs may be considered source as long as there is evidence of the visit in the subject's record. The eCRF can be source for the following data collection points: the subject number, inclusion criteria "Subject (or the legal guardian) is willing to sign informed consent form", exclusion criteria "Pregnant or breast feeding women, or women of child bearing potential and who are not on a reliable form of birth control" and "Subject is enrolled in one or more concurrent studies that would confound the results of this study", the date the study center became aware of the AE/Death, check boxes on AE CRF for "Prolongation of existing hospitalization" and "Device interrogation", "Device reprogramming" on AE CRF, and "Location of subject at time of death" on death CRF. Even when the CRF may be considered as source, an alternate method of source documentation is always strongly encouraged.

More details regarding data management will be described in the Data Management Report.

## Appendix A: Study Overview

|                         |                                                                                                                                                                                                                                                                                                                                                                                                                                                                                                                                                                                                                                                                                                                                                                                                                                                                                                                                                                                                                                                                                                                                                                                                                                                                                                                                                                                                                                                                                                                                                                                                                                                                                                                                                                                                                                                                                                                                                                                                                                                                                                                                                                                                                                                                                              |
|-------------------------|----------------------------------------------------------------------------------------------------------------------------------------------------------------------------------------------------------------------------------------------------------------------------------------------------------------------------------------------------------------------------------------------------------------------------------------------------------------------------------------------------------------------------------------------------------------------------------------------------------------------------------------------------------------------------------------------------------------------------------------------------------------------------------------------------------------------------------------------------------------------------------------------------------------------------------------------------------------------------------------------------------------------------------------------------------------------------------------------------------------------------------------------------------------------------------------------------------------------------------------------------------------------------------------------------------------------------------------------------------------------------------------------------------------------------------------------------------------------------------------------------------------------------------------------------------------------------------------------------------------------------------------------------------------------------------------------------------------------------------------------------------------------------------------------------------------------------------------------------------------------------------------------------------------------------------------------------------------------------------------------------------------------------------------------------------------------------------------------------------------------------------------------------------------------------------------------------------------------------------------------------------------------------------------------|
| Title            | Left Ventricular MultiSpot Pacing for CRT (iSPOT)                                                                                                                                                                                                                                                                                                                                                                                                                                                                                                                                                                                                                                                                                                                                                                                                                                                                                                                                                                                                                                                                                                                                                                                                                                                                                                                                                                                                                                                                                                                                                                                                                                                                                                                                                                                                                                                                                                                                                                                                                                                                                                                                                                                                                                     |
| Study Purpose    | This clinical trial is a feasibility, prospective, interventional, non-randomized multi-center research study evaluating contractility using positive left ventricular (LV) $dP/dt$ max between various LV pacing site(s) in patients indicated for cardiac resynchronization therapy (CRT).                                                                                                                                                                                                                                                                                                                                                                                                                                                                                                                                                                                                                                                                                                                                                                                                                                                                                                                                                                                                                                                                                                                                                                                                                                                                                                                                                                                                                                                                                                                                                                                                                                                                                                                                                                                                                                                                                                                                                                                                 |
| Background       | 
CRT has been one of the most important advancements in the past decade for patients with systolic heart failure (HF) and a wide QRS. Several clinical trials have shown improvements in mortality [1, 2], exercise capacity [1], clinical symptoms [2, 3], and quality of life (QOL). However, only approximately 70% of the CRT patients show benefit from the therapy. Multiple reasons for such a low responder rate have been proposed, such as underlying HF severity and etiology, suboptimal device programming, inadequate viable myocardium, lack of baseline dyssynchrony, and non-optimal LV lead position [1-3]. Recent efforts to increase the responder rate is to pace from multiple sites [4]. Multi-site pacing can be achieved either by the introduction of a second LV or right ventricular (RV) lead [5-10] or by additional electrodes on one lead (e.g. Quadripolar system) [11-13]. In a study by Leclercq and coworkers, patients randomized to dual LV pacing had significantly higher LV ejection fraction and smaller LV end-systolic volumes than those randomized to standard BiV (single LV) pacing in the posterolateral or lateral vein [7]. However, there was no difference in the primary endpoints of QOL and 6 minute hall walk. The use of one-lead with multiple electrodes has recently been investigated in more detail with regard to improving (hemodynamic) response in CRT patients. However, it has been shown that the acute hemodynamic response within one vein is not enhanced by using more spots simultaneously (Multispot) [14]. Recently the importance of a two LV lead system was compared to a Multispot configuration. Multispot pacing alone did not improve the positive <math>dP/dt</math> max when compared to standard BiV pacing, but Multispot pacing using an additional LV lead did increase positive <math>dP/dt</math> max [15].
 
The iSPOT study will evaluate three different configurations (BiV, MultiVein and, MultiSpot) and hypothesize that the positive LV <math>dP/dt</math> max achieved by the one-lead multiple electrode configuration (MultiSpot) or two-vein configuration (MultiVein) will be similar to that achieved by the current standard BiV lead configuration (non-inferiority).
 |
| Study Components | 
The following components will be used in the study:
 
 
• Medtronic hand-held pacer
 
• Right atrial, right ventricle and left ventricle leads
 
                                                                                                                                                                                                                                                                                                                                                                                                                                                                                                                                                                                                                                                                                                                                                                                                                                                                                                                                                                                                                                                                                                                                                                                                                                                                                                                                                                                                                                                                                                                                                                                                                                                                                                                                                                                                                                                                                                                                                                                                                                                                                   |

|                     |                                                                                                                                                                                                                                                                                                                                                                                                                                                                                                                                                                                                                                                                                                                                                                                                                                                                                                                                                                                                                                                                                                                                               |
|---------------------|-----------------------------------------------------------------------------------------------------------------------------------------------------------------------------------------------------------------------------------------------------------------------------------------------------------------------------------------------------------------------------------------------------------------------------------------------------------------------------------------------------------------------------------------------------------------------------------------------------------------------------------------------------------------------------------------------------------------------------------------------------------------------------------------------------------------------------------------------------------------------------------------------------------------------------------------------------------------------------------------------------------------------------------------------------------------------------------------------------------------------------------------------|
